### Objectives

The primary aim of this project is to implement and sustain improvements in post-diagnosis care for people with dementia and their carers by increasing adherence to three key recommendations from the *Clinical Practice Guidelines for Dementia in Australia* [2]:People with dementia living in the community should be offered occupational therapy (reflecting evidence-based programs)People with dementia should be strongly encouraged to exerciseCarers and family of people with dementia should have access to programs that provide respite and support to optimise their ability to provide care for the person with dementia.

This will be achieved by establishing three nationwide QICs (of approximately ten health professionals and their sites each) who regularly work with people with dementia and their carers. The three guideline recommendations were chosen to be implemented because adherence to them is known to be poor. Occupational therapy intervention involving home modification, education, problem solving, and activity engagement is shown to be cost-effective [18], yet in practice occupational therapists focus on assessment at the expense of intervention [19]. People with dementia are not routinely encouraged to exercise or participate in physical activity [20] despite exercise being the most effective intervention demonstrated to delay functional decline [21]. Supporting carers of people with dementia to maintain their wellbeing and to independently problem solve and manage their own needs can reduce negative carer impacts as well as delaying functional decline and reducing the occurrence of changed behaviours in the person they care for [22, 23]. Yet these types of programs are not widely available, and carers report that they need more education, skills counselling, respite, and emotional support to help them in their caring role [24, 25]. Implementation of these guideline recommendations reflects the priorities of people with dementia and carers, who have called for improved post-diagnostic care which facilitates independence and social engagement for people with dementia and provides effective support for their carers [26]. The recommendations are low-cost, acceptable, and feasible interventions that reflect broader policies around healthy ageing [27].

The secondary aim of this project is to assess the impact of the QIC on experiences and outcomes for people with dementia and their carers.

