Client dyads will be existing patients with dementia and/or their carers within the caseload of the implementation clinician at the implementation site. Strict inclusion criteria will not be applied, and implementation clinicians will be asked to use their judgement; eligible people with dementia will be any client with a diagnosis of dementia (or suspected dementia) who attends a consultation with or without a carer. Carers will be any person attending the consultation who provides substantive care for a person with dementia and identifies as a carer. Implementation clinicians will complete the checklists about their consultation with each person with dementia (or carer, or dyad, where applicable) they see and return these to the study team. They will also ask for verbal assent (from both members of the dyad, where applicable) to pass contact details onto the study team for the purposes of two follow-up phone interviews. The study team will randomly select one dyad (per clinician) from among those assenting each month to receive these phone interviews (details below), for a total of 180 dyads.

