#### Service and client-level outcomes

During the client dyad phone interview up to 5 weeks after the consultation, both the person with dementia (where applicable) and their carer will be asked to rate their satisfaction with the consultation using an amended version of the Patient Satisfaction Questionnaire Short-Form (PSQ-18) [58]. Seven PSQ-18 items were selected because they were relevant to the types of consultations delivered by QIC clinicians. They assess satisfaction with the time spent with the health professional and their communication and interpersonal manner on a 5-point Likert scale (total score range 7–35). Items on the PSQ-18 have adequate internal consistency (all >  0.65) [58].

Adverse events that may reflect the safety of the QIC model will be reported by implementation clinicians during monthly QIC meetings and in in-depth interviews. Client dyads will also be asked to reflect on the recommendations made during the consultation by the implementation clinician and report any negative consequences.

We will also assess the impact of the QIC model and guideline adherence on quality of life for the person with dementia (clients of clinicians in the exercise and occupational therapy QICs) or burden for the carer (clients of clinicians in the ‘carer support’ QIC) during this phone interview. These outcomes will be assessed a second time with a follow-up phone interview up to 7 weeks after the first, to identify sustained impact.

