### Analysis

#### Quantitative analysis

Guideline adherence and client outcomes over time will be evaluated with a segmented regression analysis using the PROC NLIN function of SAS version 13.2 [63]. This technique uses modelling to draw conclusions about an outcome (in this case guideline adherence) across distinct segments of time (in this case, before and after quality improvement implementation) [64]. Data points for the time series will be the extent of guideline adherence each month over 18 months. Potential confounding variables will be fitted as covariates, and the most parsimonious model will be determined via stepwise backward elimination. The hypothesised outcomes of interest for this study are level and trend changes reflecting increasing adherence to the relevant guideline recommendation after the intervention (post-education quality improvement implementation) and over the 18 months. We will also calculate the counterfactual value and its proportionate distance from the actual estimated value [65]. The PROC AUTOREG function will be used to control for autocorrelation [63].

The sample size calculation for segmented regression analysis is related to the estimated number of time points at which data will be recorded. It is necessary to have enough time points before and after the intervention. This study incorporates 18 months of data collection (9 months pre-intervention and 9 months post-intervention) and is powered at 83% to detect a minimum 15% change in guideline adherence based on an estimated effect size of 1, autocorrelation of 0.3, and *α* = 0.05 [66]. This change in guideline adherence was used for power analysis based on literature suggesting an average of 10–15% improvement in adherence from traditional guideline dissemination activities [7]. Per recommendations from Wagner et al. [65], clinicians will submit up to ten checklists for each data point in the time series (for a total of up to 300 checklists each month) to achieve an acceptable level of variability of the estimate at each time point. The study design therefore meets the criteria for a robust interrupted time-series [67].

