Despite these strengths, the approach for this study has some important limitations. First, the inclusion of a control group was considered unethical because clients would be deprived of best-practice care, and engaging clinicians to provide data without any intervention would be difficult. Effects occurring at the same time but separate to the intervention will not be separated and controlled for, threatening validity. Nonetheless, even without a control group, segmented regression analysis makes multiple assessments of the outcome and therefore addresses important threats to internal validity. Second, the primary outcome measure (guideline adherence) will be self-reported by the implementation clinicians and is therefore vulnerable to a responding bias. The triangulation of data from client dyad phone calls will help to address this problem, and adherence (according to the criteria described in Table 3) will be independently judged by two members of the research team and an external third party where needed based on clinician reported ‘snapshots’ of the consultation. Nonetheless, some responding bias may still exist. Third, a selection bias may be present in the participating implementation clinicians. The ‘opt-in’ approach to recruitment will likely lead to a group of passionate and engaged clinicians who may not represent the wider population of clinicians working with people with dementia and their carers. Finally, there are some limitations associated with segmented regression analysis. These models assume a linear trend in the outcome within each segment, but this may not hold over longer intervals [65]. Segmented regression analysis also does not allow for statistical controlling of individual-level covariates. However, these covariates will only become confounding where they both predict the outcome and change in relationship to the time of the intervention. No such covariates are anticipated.

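### Two calls made after the consultation, in windows with no lower limit, cannot by themselves show sustained impact; the before/after contrast can, but it is not protected against shifts in case mix and call timing.

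*Protocol article*

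**What the plan says.** The Objectives state: "The secondary aim of this project is to assess the impact of the QIC on experiences and outcomes for people with dementia and their carers".

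Under Service and client-level outcomes, satisfaction is asked "During the client dyad phone interview up to 5 weeks after the consultation". The same call (call 1) carries the client outcomes: "We will also assess the impact of the QIC model and guideline adherence on quality of life for the person with dementia", by DEMQOL-Proxy in the exercise and occupational therapy collaboratives, or carer burden by the 12-item Zarit interview in the carer support collaborative. The second call (call 2) is given one purpose: "These outcomes will be assessed a second time with a follow-up phone interview up to 7 weeks after the first, to identify sustained impact". The article describes no score taken before the consultation.

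On who is called, Participants says: "Client dyads will be existing patients with dementia and/or their carers within the caseload of the implementation clinician". One assenting dyad per clinician is drawn at random each month, and the total is put at 180.

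On analysis, Quantitative analysis says: "Guideline adherence and client outcomes over time will be evaluated with a segmented regression analysis". There are 9 months before and 9 after the intervention. The monthly data point is defined for adherence only. The Discussion adds: "Segmented regression analysis also does not allow for statistical controlling of individual-level covariates". It then says that such covariates confound only if they predict the outcome and also shift with the intervention, and that none are expected to. Process evaluation, however, plans to examine whether services came to reach clients who had been underserved.

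**The concern.** The first score is taken after the consultation, at a delay that can differ from dyad to dyad. The second is taken after a gap that can also differ. The dyads are existing clients at any stage of a condition that the Background calls progressive. A comparison of the two calls then has no reference: it shows what happened between two arbitrary points after the event.

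The before/after comparison does have a reference, namely dyads seen in the pre-intervention months. But different people are called each month, and the planned series, by the article's own account, cannot adjust for who they are. If the collaborative changes who is seen, or if interview delay drifts, the difference enters the estimate as a level or trend change. The secondary aim could then be answered wrongly in either direction.

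**Working it through.** The article gives no sample size or power for quality of life or burden, so there is no stated figure to reproduce. Its 83% power refers to adherence. The check covers timing, confounding and precision.

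**1. Windows** (Service and client-level outcomes)
- Call 1: 0 to 5 weeks after the consultation.
- Gap to call 2: 0 to 7 weeks.
- Call 2: 0 to 5 + 7 = 12 weeks after the consultation.

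As worded, one dyad's call 2 may come sooner after its consultation than another's call 1. DEMQOL-Proxy asks about the preceding week, so a call in the first 7 days partly describes time before the consultation.

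**2. What change between calls can show**
An unchanged score fits three accounts: a benefit reached by call 1 and kept; no effect at either call; or a benefit offset by decline. With no untreated course over the same gap, the two scores cannot tell these apart.

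**3. What the before/after contrast can show**
The intervention is the collaborative, not the single consultation. Dyads from pre-intervention months, measured in the same windows, are the reference, so no pre-consultation score is needed. The contrast requires that case mix and call delay do not shift at the interruption. If the share of a client type changes by *p* and its mean score differs by *d* from that of the others, the unadjusted contrast moves by *p* × *d*. A sudden shift appears as a level change and a gradual one as a trend change. The Discussion expects no such shift, whereas Process evaluation looks for one in reach.

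**4. Calls that cross the boundary**
Nine months is 9 × 52/12 = 39 weeks. Education follows the pre-intervention period (Educate) and takes 8 weeks (Table 1).
- Boundary at the start of education: consultations in the last 12 weeks can have call 2 after it, 12/39 = 31%.
- Boundary at the end of education: 12 − 8 = 4 weeks, 4/39 = 10%.

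Both are maxima, reached only if calls fall at their latest limits.

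**5. Precision of monthly points**
The article supports two dyad counts: the stated 180, and 30 clinicians × 18 months = 540 at one dyad per clinician per month. Assume equal collaboratives and an even spread over months. The standard error of a monthly mean is SD/√n.

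| Total dyads | Zarit per month | SE | DEMQOL-Proxy per month | SE |
|---|---|---|---|---|
| 180 | 60/18 = 3.3 | 0.55 SD | 120/18 = 6.7 | 0.39 SD |
| 540 | 180/18 = 10 | 0.32 SD | 360/18 = 20 | 0.22 SD |

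With an assumed Zarit SD of 10 on the 0 to 48 scale, the Zarit values are 5.5 and 3.2 points; they scale in proportion to the SD.

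**6. Detectable before/after difference**
Assume an even split over periods, independent observations, a plain two-mean comparison, 80% power and two-sided 0.05. The difference is (1.96 + 0.84) × √(2/n per period).
- 180 dyads: Zarit 30 v 30, 2.80 × √(2/30) = 0.72 SD; DEMQOL-Proxy 60 v 60, 2.80 × √(2/60) = 0.51 SD.
- 540 dyads: Zarit 90 v 90, 2.80 × √(2/90) = 0.42 SD; DEMQOL-Proxy 180 v 180, 2.80 × √(2/180) = 0.30 SD.

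Trend terms and clustering by clinician would raise these.

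**The case against.** The best defence is that the before/after regression already answers the impact question, and this is right. A reader might infer from the missing starting value that no impact can be shown at all. The documents do not support that, because pre-intervention dyads are the reference. Nor does progression within a dyad bias a comparison of different dyads drawn the same way from the same clinicians' caseloads. The article gives no rate of decline over at most 7 weeks, and on the Zarit scale a fall means less burden.

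The article also discloses the limit on individual-level adjustment, says no confounding covariate is expected, and plans to fit potential confounders as covariates. That stands as disclosure. But in a series of monthly values such covariates can enter only as monthly aggregates, and the expectation of no shift sits badly with a plan to examine whether reach improved. No actual shift in case mix has been shown; the point is that the plan could not handle one.

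Target call days and the model role of call-2 scores may be set out in a full protocol or analysis plan that is not shown, so their absence alone is no fault. What the article does state is the purpose of call 2, two calls both after the consultation, and an analysis without individual-level covariates.

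A tempting remedy is to treat call 1 as a baseline and adjust call 2 for it. That would do harm: existing clients in the post period may already have had changed care before the index consultation, so call 1 can carry part of the effect sought. A bare before/after term would likewise give up the control of prior trend that the Discussion names as a strength.

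**Conclusion.** The concern holds in limited form. Change from call 1 to call 2 does not identify sustained impact, whatever the windows turn out to be, because both calls follow the consultation and there is no comparison course between them. The collaborative's impact on client outcomes can be estimated from the before/after contrast, but as planned this rests on case mix and call timing staying stable, and the article secures neither.

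Up to 31% of pre-period weeks can have a second call after education starts, or about 10% if the boundary is the end of education. These are upper limits that assume the latest permitted calls. Monthly means are noisy for this purpose, with a Zarit standard error of 0.32 to 0.55 SD depending on which dyad count applies. That is a reason to analyse dyads rather than means, not evidence about the windows. The issue concerns the stated secondary aim and leaves the primary adherence outcome untouched.

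**What to change.** Keep the two calls and the instruments, and change four things.

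1. **Model.** Analyse client outcomes at dyad level with a segmented mixed model that keeps the level and trend terms, has a clinician random effect, and adjusts for dyad characteristics that the collaborative cannot affect. This replaces the series of monthly means.
2. **Estimand.** Estimate the before/after contrast separately at call 1 and at call 2, without adjusting call 2 for call 1. Define sustained impact as the contrast at call 2.
3. **Windows.** Set target windows with a minimum gap for both calls (consultation to call 1, and call 1 to call 2), the same in both periods.
4. **Boundary.** Classify dyads by the date of the index consultation. Exclude from the pre-intervention period call-2 scores obtained after education starts, or handle them in a sensitivity analysis.

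The 180 and 540 dyad counts should be reconciled at the same time, so that coverage of both periods is clear.

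The cost is tighter call scheduling, some missed windows and slightly more analysis work. The adjustment characteristics must be recorded if they are not already. Adjustment deals only with what is recorded, so some risk from unmeasured case mix remains.

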### Analysis

#### Quantitative analysis

Guideline adherence and client outcomes over time will be evaluated with a segmented regression analysis using the PROC NLIN function of SAS version 13.2 [63]. This technique uses modelling to draw conclusions about an outcome (in this case guideline adherence) across distinct segments of time (in this case, before and after quality improvement implementation) [64]. Data points for the time series will be the extent of guideline adherence each month over 18 months. Potential confounding variables will be fitted as covariates, and the most parsimonious model will be determined via stepwise backward elimination. The hypothesised outcomes of interest for this study are level and trend changes reflecting increasing adherence to the relevant guideline recommendation after the intervention (post-education quality improvement implementation) and over the 18 months. We will also calculate the counterfactual value and its proportionate distance from the actual estimated value [65]. The PROC AUTOREG function will be used to control for autocorrelation [63].

The sample size calculation for segmented regression analysis is related to the estimated number of time points at which data will be recorded. It is necessary to have enough time points before and after the intervention. This study incorporates 18 months of data collection (9 months pre-intervention and 9 months post-intervention) and is powered at 83% to detect a minimum 15% change in guideline adherence based on an estimated effect size of 1, autocorrelation of 0.3, and *α* = 0.05 [66]. This change in guideline adherence was used for power analysis based on literature suggesting an average of 10–15% improvement in adherence from traditional guideline dissemination activities [7]. Per recommendations from Wagner et al. [65], clinicians will submit up to ten checklists for each data point in the time series (for a total of up to 300 checklists each month) to achieve an acceptable level of variability of the estimate at each time point. The study design therefore meets the criteria for a robust interrupted time-series [67].

Feasibility data elicited from field notes and records will be provided descriptively so that it is possible to determine how many people expressed interest, how many formally participated, and how many people withdrew (and reasons for withdrawal). We will present information about the characteristics of the clinicians and their workplaces. We will also describe engagement and exposure to the intervention through presentation of time spent participating in the online training and participation in other components of the intervention such as number of contributions to the online community of practice and completion of the implementation plan. Data from the NOMAD and QIKAT tools regarding implementation readiness and proficiency will be presented descriptively (with means and standard deviations where appropriate).

The mixed sources of data will be used to explore factors underlying successful implementation. The percentage increase in average guideline adherence during the 9-month pre- and post-intervention periods will be calculated for individual clinicians, to represent implementation success. *T* or correlation tests (where appropriate) will be used to identify the impact of workplace characteristics, time engaged in the intervention, and NOMAD/QIKAT scores on implementation success. Qualitative data will be used to explore and contextualise the findings.

A cost-benefit analysis will be used for the economic evaluation [54]. The costs associated with establishing and running the QIC will be compared to the monetary benefits of implementing this strategy. The QIC will be considered value for money (i.e. cost-beneficial) if benefits exceed costs. Benefits will be considered from the perspective of implementation clinicians’ point of view. The return on investment will also be estimated as the ratio of benefits divided by total costs of the intervention (i.e. the benefit-cost ratio) [54].

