## Methods

### Design

An overview of the project per guidelines by Proctor et al. [28] appears in Table 1. The impact of QICs on guideline implementation and outcomes for people with dementia and carers (‘client dyads’) will be evaluated in this implementation research project using an interrupted time-series design [29]. Interrupted time series is a strong evaluative design for estimating the impact of an intervention in non-randomised settings because it allows for detailed assessment of longitudinal trends associated with an intervention [30]. Feasibility, acceptability, cost-effectiveness, and sustainability of the model will be evaluated using an inbuilt mixed-methods process evaluation [31]. Both administrative data and data collected from participating health professionals, their employing organisations, and their clients with dementia and carers will inform the outcomes for this study.

**Table 1 Tab1:** Overview of project per guidelines by Proctor et al. [28]

Action	Description
Name it	Establishment of QICs to improve care for people with dementia and their carers
Define it	QICs enable rapid, sustainable improvements in care by bringing together health services to learn together, share ideas, and benchmark outcomes
Specify it	
a) The actor	The project team establishes and supports the QICs; Implementation clinicians form the QICs and conduct quality improvement (using PDSA cycles)
b) The action	Completion of an online training course, development of a site-specific implementation plan, and enactment of this plan (using PDSA cycles)
c) Action target	“Implementation clinicians”: health professionals across Australia who have some leadership responsibilities yet are still closely connected to the delivery of services and can introduce changes to practice
d) Temporality	The clinicians will participate in online training, develop a sites-specific implementation plan, and then enact the plan.
e) Dose	Seven education modules of 2 hours each, to be completed over 8 weeks; 11 virtual QIC meetings
f) Implementation outcome affected	Primary outcome: adherence to recommendation as described in the criteria in Table 3.
g) Justification	The intervention was designed to match with factors known to enable evidence-based care for people with dementia and their carers and to be relatively ‘light touch’ and promote rapid change

*Abbreviations*: *PDSA* plan-study-do-act, *QIC* quality improvement collaborative

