#### Educate

Education for implementation clinicians will be delivered after a 9-month pre-intervention period and include written resources, webinars, expert feedback, collaboration and peer supervision, and online learning. The main component of the education will be an intensive, eight-module ‘massive open online course’ (MOOC) to upskill implementation clinicians on the clinical evidence base related to occupational therapy for people with dementia, physical activity for people with dementia, or carer support. The MOOC will focus on quality improvement techniques in clinical settings. Implementation clinicians will be guided through the development of an associated implementation plan unique to their service context and informed by service gaps and barriers and facilitators to improvement identified during the planning phase. The MOOC will be co-designed with people with dementia and carers to ensure it reflects their needs and experiences. Input will also be sought from clinical, aged care industry, quality improvement, and educational design experts to ensure it is rigorous, up-to-date, and effectively facilitates learning. Implementation clinicians will have access to people with dementia, carers, and clinical and quality improvement experts to review their plan and provide feedback. A peer review process will also allow implementation clinicians to give and receive feedback from another member of their QIC.

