#### Quality management

Once reviewed, clinicians will implement their plan and participate in monthly virtual meetings with their QIC to benchmark and brainstorm strategies to overcome any noted roadblocks. They will iteratively review and update their plans using PDSA cycles [47] with support from people with dementia and carers and clinical and quality improvement experts. Clinician reports of the consultation will be audited, cross-referenced with client dyad reports, and anonymously fed back to facilitate self-assessment.

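### Unadjusted tests of time engaged against adherence gain can show an association, not the impact that the plan says they will identify

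*Protocol article*

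**What the plan says.** The test is described in the protocol article under Quantitative analysis. The outcome is defined first: "The percentage increase in average guideline adherence during the 9-month pre- and post-intervention periods will be calculated for individual clinicians, to represent implementation success". Candidate factors are next compared with this gain, using t or correlation tests that "will be used to identify the impact of workplace characteristics, time engaged in the intervention, and NOMAD/QIKAT scores on implementation success". No covariate, lag or baseline measure of motivation is stated for these tests.

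The same section describes engagement as "time spent participating in the online training and participation in other components of the intervention such as number of contributions" (meaning posts in an online community), and it also lists finishing the implementation plan. It does not say which of these make up time engaged, or over which months.

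On timing, the Educate section states: "Education for implementation clinicians will be delivered after a 9-month pre-intervention period". Table 1 gives the planned dose: "Seven education modules of 2 hours each, to be completed over 8 weeks; 11 virtual QIC meetings". Under Quality management, "clinicians will implement their plan and participate in monthly virtual meetings with their QIC", and audited consultation reports are returned to clinicians so that they can assess themselves.

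The abstract's discussion and the last paragraph of the Discussion say that the study will establish which elements of the strategy contributed to adherence. The limitations note that opt-in recruitment "will likely lead to a group of passionate and engaged clinicians", but treat this only as a question of representativeness.

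**The concern.** Identifying an impact requires that clinicians who engaged more and those who engaged less would otherwise have improved equally. Two features of the design work against this.

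- **Common cause.** Motivated clinicians may both spend more time in the programme and improve their practice more. This applies to every component, including training.
- **Reverse causation.** A clinician whose plan is working has reason to keep attending and posting, and one who is struggling may drop away. This applies to components that run alongside the outcome months.

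Both push the correlation upward. At stake is the conclusion about which elements contributed. A positive result could be taken as evidence that more contact with the collaborative raises adherence when it shows no such thing.

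**Working it through.** The plan gives no figure for this test, so there is none to reproduce. The timing was checked by reading, and the possible size by illustration.

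**1. Timing.** Follow-up is 9 months before and 9 months after the intervention. Education follows the pre-period and lasts 8 weeks; monthly meetings accompany implementation. Meetings, forum use and plan work therefore fall largely within the 9 outcome months. Training may fall in roughly the first two of them, or before them if the post-period starts once education ends.

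**2. Motivation as common cause.** From the document: n = 30 clinicians. Assumed: a two-sided 5% level (none is stated for this test), no true effect of engagement, and motivation correlated *a* with engagement and *b* with gain.

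- Expected spurious correlation: r = a × b.
- Critical value: t(0.975, 28 df) = 2.048, so r = 2.048 / √(28 + 2.048²) = 0.361.
- Approximate rejection rate by Fisher's transformation: compare atanh(r) × √27 with 1.96.

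| a = b | r | atanh(r) × √27 | Approx. significant | Simulated |
|---|---|---|---|---|
| 0 | 0 | 0 | 5% | 5% |
| 0.3 | 0.09 | 0.47 | 8% | 8% |
| 0.5 | 0.25 | 1.33 | 26% | 27% |
| 0.7 | 0.49 | 2.79 | 80% | 81% |

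**3. Early success driving later engagement.** Assumed: between-clinician SD of true adherence change 10 points; monthly noise SD 16 points; each month's change correlated *g* with the next month's engagement; engagement summed over 9 months; no effect of engagement on adherence.

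- Variance of one month's change: 100 + 256 = 356, SD 18.87.
- Variance of the 9-month mean change: 100 + 256/9 = 128.4, SD 11.33.
- Covariance of summed engagement with mean change (8 driven months): 8 × g × 128.4 / 18.87 = 54.5g.
- Variance of summed engagement: 9 + 56 × g² × 100/356 = 9 + 15.73g².
- Expected r = 54.5g / (11.33 × √(9 + 15.73g²)).

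| g | r by formula | Simulated mean r | Simulated significant |
|---|---|---|---|
| 0 | 0 | 0.00 | 5% |
| 0.1 | 0.16 | 0.15 | 13% |
| 0.2 | 0.31 | 0.31 | 38% |
| 0.3 | 0.45 | 0.44 | 72% |
| 0.5 | 0.67 | 0.66 | 99% |

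**4. What fixing the exposure early changes.** In step 3, using only engagement at the start of the post-period returns the false-positive rate to about 5% at every *g*. Step 2 does not change: early engagement is also driven by motivation, so the same *a* and *b* give the same rates.

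**The case against.** The strongest reply is that the article does not define time engaged as meetings and posts. The only engagement measure it expresses as time is time in the online training. The analysis describes the intervention as implementation after education, so training could precede the whole outcome window. A reader might infer that exposure and outcome cover the same 9 months throughout. The documents do not support that: no window is fixed, and the Intervention section speaks of engagement over 18 months. This stands, and it limits reverse causation to the continuing components.

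The correlations are assumed. At 0.3 the false-positive rate is close to nominal, and an opt-in group of keen clinicians may vary little in motivation, which would weaken the effect. Engagement is also partly set by a planned dose and a formal research agreement. These points stand too, so the figures show a range and do not predict an error rate.

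The analysis is introduced as exploring factors behind successful implementation and is put in context by qualitative data. The claims about contributing elements can also draw on interviews, the NoMAD survey and field notes. A reader might infer that a false effect of dose will be concluded, or that this correlation will decide how much contact to offer. The article says neither. It does state that these tests will identify an impact, and neither the exploratory framing nor the stated limitations withdraws that.

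**Conclusion.** The point holds in a limited form. A bivariate test of self-selected engagement against adherence gain cannot separate an effect of engagement from motivation, nor, for components that run during the outcome months, from early success. The stated limitations do not mention this.

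Under the assumptions shown, confounding by motivation alone makes a nominal 5% test significant in about 8% to 81% of trials with no true effect. Feedback from early success gives 13% to 99% for *g* from 0.1 to 0.5, if time engaged is summed over the post-period. None of the correlations or SDs comes from the documents.

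This is a secondary process analysis. A reader might carry the criticism over to the main result, but the primary segmented regression does not use individual engagement and is unaffected. The change is still worth making, because it alters what the trial may conclude about its components.

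**What to change.** - Describe the tests as examining the association of time engaged with implementation success, keep them labelled exploratory, and name motivation and early success as alternative explanations. Do not use the result alone to support the statement that a component contributed to adherence.
- Define time engaged and its window. Where records are dated, use engagement fixed by the end of the education period (training completed, plan submitted) and relate it to adherence in later months. Present meeting attendance and forum use in the post-period descriptively.

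The wording change costs nothing. The time-ordered exposure depends on dated records, which the article does not confirm. Early engagement probably varies less between clinicians, so the estimate loses some precision. If the 8 weeks of education fall inside the post-period, about two of the nine outcome months are lost to this analysis. It removes reverse causation only, so the wording change is needed in either case.
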